### Objectives

The study aimed to determine the safety of metformin 1000 mg, AP capsules 1000 mg, and AP capsules 2000 mg in the clinical part.

In the pharmacokinetics and metabolomics analyses, metformin 1000 mg will be used as a model drug for the determination of the pharmacokinetic parameters including the Cmax, Tmax, half-life (T1/2), and AUC0-infinity. The individualised Cmax of metformin will be used for the metabolomics analyses to identify dysregulated human metabolic pathways that are associated with diabetic effects.

The AP 1000 mg and AP 2000 mg analyses will follow the pharmacokinetics and metabolomics framework from the metformin arm in the second analysis. The pharmacokinetics for AP 1000 mg and AP 2000 mg will be compared for the three bioactive compounds, andrographolide, neoandrographolide, and deoxyandrographolide. The dysregulated human metabolic pathways identified from the metabolomics analyses for two doses will be compared based on the dose-dependent effects. 

Finally, the dysregulated human metabolic pathways associated with the diabetic effects will be compared for all three intervention arms.

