The rationale of metformin selection as a model drug includes the well-known safety profiles of the first line antihyperglycemic drug and its inconclusive mechanism of action. There have been several metabolomics analyses for metformin on healthy volunteers and patients, and the perturbed human metabolic pathways associated with the pharmacodynamics effects remain inconsistent [29]. Therefore, this study focussed on the individualised pharmacokinetic guided Cmax samples to investigate the dysregulation of metabolic pathways under a controlled environment. The AP capsule is a traditional medicinal product registered under the Ministry of Health Malaysia for general well-being [30]. Several clinical trials conducted have demonstrated the effects on diabetes, ulcerative colitis, and upper-respiratory tract infections [19,31,32]. Most of the traditional herbal medicine could not provide evidence of the pharmacokinetics of multi-components in the drug development process. Kantae et al. proposed that the discovery of metabolite biomarkers using pharmacometabolomics could predict the pharmacokinetic and pharmacodynamic effects [33]. Therefore, this proof-of concept crossover study was designed to investigate individualised pharmacokinetic and pharmacometabolomic studies on metformin in the first analysis set as a model drug, followed by AP using a similar analysis framework in the second analysis set with additional dose-dependent effects. The dysregulated human metabolic pathways associated with the diabetic effects for the three investigational products were then compared.

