### 3.3. Untargeted Metabolomics and Multivariate Data Analysis

In the metformin analyses, pharmacometabolomics analysis will be performed to explore the human metabolic pathways between the pre-dose and peak plasma concentration. The samples will be analysed using Agilent LCMS-QTOF for an untargeted metabolomics approach following the literature method with some modification [47]. The samples will be analysed using a reverse phase column with a guard column in both the positive and negative modes. The instrument method setting will follow the METLIN analysis methods [48]. The pool quality control samples will be used to condition the column and visualisation checking for the batch analysis.

The untargeted metabolomics workflow is presented in Supplementary Figure S8. The chromatograms will be converted to the mzXML file using Global Natural Products Social (GNPS) package, University of California San Diego, California, United States [49]. MS spectral processing, normalisation, batch correction, multivariate analysis, and functional metabolic pathway analysis will be run on MetaboAnalyst web-based application (McGill University, Montreal, QC, Canada) to identify the human metabolic pathways [50]. In the multivariate analyses, principal component analysis (PCA) and partial least square discriminant analysis (PLSDA) will be used to inspect the region’s separation among the analysed time points. After this, a t-test will be used to identify the significantly differentiated compounds between the two-time point groups. The significant features will be processed in MS peaks to a pathway module to identify the dysregulated human metabolic pathways according to the Kyoto Encyclopaedia of Genes and Genomes (KEGG) database.

A similar analysis framework for metformin as described above will be repeated for AP 1000 mg and AP 2000 mg. There will be a head-to-head comparison of the pharmacokinetic profiles for both the AP arms. After this, the pharmacometabolomic identified dysregulated human metabolic pathways will be compared for the two doses in AP to investigate the dose-dependent effects. Finally, the dysregulated human metabolic pathways associated with the diabetic effects for the metformin, AP 1000 mg, and AP 2000 mg will be compared.

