### 3.4. Reporting Framework

The study will be designed to use metformin as a model drug in the application of targeted peak plasma concentration in the metabolomics study. The clinical safety data, method validation, pharmacokinetics and metabolomics results of metformin will be reported in detail. This report suggests an application model for individualised pharmacokinetics and pharmacometabolomics study in an early-phase clinical trial in the drug development program. The results and the proposed pharmacometabolomic application framework in an early-phase clinical trial for the first analysis using metformin was recently published [51].

In the second report, the pharmacokinetics profiles for AP 1000 mg and AP 2000 mg will be presented. The results will include the dose-dependent effects of the dysregulated human metabolic pathways associated with the pharmacological effects. This report will suggest another application model for the pharmacokinetics and pharmacometabolomics study using multi-component herbal medicines in an early-phase clinical trial. Additional dose-dependent effects will be described in the report. Finally, the dysregulated human metabolic pathways associated with the diabetic effects will be compared for metformin and AP.

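### The closing three-arm comparison covers only pathways already flagged within an arm, so unflagged diabetes-related pathways drop out and arms with the same effect can look different

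*Protocol article*

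**What the plan says.** Section 3.3 sets out a chain of selections. Within an arm, "a t-test will be used to identify the significantly differentiated compounds between the two-time point groups". Next, "The significant features will be processed in MS peaks to a pathway module to identify the dysregulated human metabolic pathways", with KEGG as the reference database. The chain is then run again for the two AP doses: "A similar analysis framework for metformin as described above will be repeated for AP 1000 mg and AP 2000 mg". The closing step is: "Finally, the dysregulated human metabolic pathways associated with the diabetic effects for the metformin, AP 1000 mg, and AP 2000 mg will be compared".

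The Objectives give the same comparison as the last aim: "the dysregulated human metabolic pathways associated with the diabetic effects will be compared for all three intervention arms". Section 3.4 repeats it for metformin and AP.

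Three other statements bear on the point:

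- The Introduction announces an interest in pathways related to antihyperglycemic effects but names none.
- Section 2.1 says that, for metformin, "the perturbed human metabolic pathways associated with the pharmacodynamics effects remain inconsistent".
- Section 3.4 says that the report "for the first analysis using metformin was recently published", while the AP report and the final comparison are still in the future tense.

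Section 2.3.6 calls the study a proof-of-concept exploration with 18 subjects per formulation and says the sample size has no statistical basis.

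**The concern.** The set of pathways to be compared is itself a result. Two consequences follow from the rule as worded.

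1. A diabetes-related pathway that no arm flags is outside the comparison. The reader cannot tell a pathway that was examined and unchanged from one that was never considered.
2. Flagging is done arm by arm, with 18 volunteers. Comparing lists of flagged pathways compares significance statuses, not sizes of change. Two treatments with the same true effect will often differ in status, and that difference could be read as a drug or dose effect.

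At stake is the trial's last objective, the only one that sets AP beside metformin on the pathways of therapeutic interest.

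**Working it through.** **No figure to reproduce.** The article gives no alpha, power, effect size or pathway count for this comparison. What follows is an illustration on stated assumptions.

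**Inputs.** From the article: n = 18 per formulation in a crossover; selection within each arm by a t-test between two time points; three arms. Assumed: a paired t-test, two-sided alpha 0.05, one summary score per pathway, the same true standardised change d in all three arms, and arms treated as independent.

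**Step 1: within-arm power.** The t statistic has 17 degrees of freedom and noncentrality d × √18. The critical value is 2.110. For d = 0.5 the noncentrality is 0.5 × 4.243 = 2.121, and power p is 0.516.

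**Step 2: disagreement between arms.** Given a flag in at least one arm, the probability that at least one other arm misses the pathway is

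[1 − p³ − (1 − p)³] / [1 − (1 − p)³]

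For p = 0.516: p³ = 0.138 and (1 − p)³ = 0.113, so the result is 0.749 / 0.887 = 0.84.

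| Assumed shared change (SD) | Power in one arm | Flagged in at least one arm but not in all three, given at least one flag |
|---|---|---|
| 0.3 | 0.22 | 0.98 |
| 0.5 | 0.52 | 0.84 |
| 0.7 | 0.80 | 0.485 |

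The same volunteers supply all arms. If their changes are positively correlated across treatments, disagreement is less frequent than shown.

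**Step 3: does a direct test on the selected set cure this?** Not fully. In a simulation of 20,000 runs, a contrast between two arms at 0.05 was limited to pathways significant in either arm. Its false-positive rate was 0.31 when neither arm had an effect, 0.10 when both shared a change of 0.3 SD, and 0.07 at 0.5 SD. Without selection it was 0.049 to 0.051. The contrast has to be made over a set chosen without regard to significance.

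**Step 4: chance flags.** Suppose m pathways could count as diabetes-related, with no true effect and independent tests. The chance of at least one flag in any of three arms is 1 − (1 − alpha)^(3m). For m = 5 to 30 this is 0.54 to 0.99 at alpha 0.05, and 0.14 to 0.60 at alpha 0.01. These values depend on the assumed m and alpha. They do not measure false agreement between AP and metformin. The chance that some pathway is flagged in both metformin and one given AP arm at 0.05 is 1 − (1 − 0.05²)^m = 0.02, 0.04 and 0.08 for m = 8, 16 and 32.

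**The case against.** The strongest reply is that this is declared exploratory work. An untargeted screen forms its findings from the data by design, and no confirmatory pathway test is claimed. That stands, and it limits the remedy to labelling and full reporting. It does not remove the selection. Section 4 also says the approach can identify pathways accurately, which is more than a screen of this kind supports.

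A second reply is that an article condenses. A pathway list, a significance threshold, a multiplicity rule or a between-arm test may sit in protocol version 4.0 of 17 September 2019, in the workflow supplement or in an analysis plan, none of which is shown. That stands too, and their absence from the article is no fault in itself. But a threshold added elsewhere would still leave a comparison restricted to flagged pathways, because the article states that restriction in three places.

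A reader might go further and infer that the diabetic label is attached once the flagged pathways are known, or that the rule was shaped by the published metformin results. The documents do not support either. No section gives the order of flagging and labelling, and the antihyperglycemic interest is announced as an aim. The remark about publication dates the article, not the rule, and the approved protocol is from 2019. Each AP arm's pathways also come from that arm's own data. Nor can anything be said here about how the published metformin report applied the label, since that report is not among the documents.

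It might also be inferred that chance pathways will become the trial's main message. The exploratory status does not support that, and the chance-flag probabilities rest on assumed inputs. Bringing that risk down to 5% would be the work of multiplicity correction, not of closing the list: five uncorrected pathways still give 1 − 0.95⁵ = 0.23 per arm.

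**Conclusion.** The point holds in a limited form. As worded in Section 3.3, the Objectives and Section 3.4, the final comparison is conditioned on within-arm significance, and the article fixes no pathway set. Unflagged diabetes-related pathways are left out, and differences in flagging between arms are a poor guide to differences in effect. At an assumed shared change of 0.5 SD, about 84% of pathways flagged somewhere would be missed in at least one other arm; the figure runs from 98% at 0.3 SD to about 49% at 0.7 SD. These values assume paired tests at two-sided 0.05, one score per pathway and independence between arms. The change is worth making while the AP analysis is still ahead, but the point does not undermine the study's exploratory purpose.

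**What to change.** Before the AP data are processed, fix in a dated addendum the KEGG pathways that count as diabetes-related and name the source of the choice. If the full protocol already contains such a set, cite it. Section 2.1 describes the metformin findings as inconsistent, so the source needs to be explicit.

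Replace the closing sentence of Section 3.3 and the matching objective with:

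*For each of these pathways the score and p-value are reported for all three treatments whether or not significant, with a direct within-subject between-treatment contrast and multiplicity correction over the set; any other flagged pathway is reported as exploratory, and the three-arm comparison is described as hypothesis-generating.*

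Bring Section 3.4 into line. The crossover already supplies the within-subject contrast, so no new samples or assays are needed. The cost is one addendum and a fixed results table. The downside is that a flagged pathway outside the set can be reported only as exploratory.

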### 3.4. Reporting Framework

The study will be designed to use metformin as a model drug in the application of targeted peak plasma concentration in the metabolomics study. The clinical safety data, method validation, pharmacokinetics and metabolomics results of metformin will be reported in detail. This report suggests an application model for individualised pharmacokinetics and pharmacometabolomics study in an early-phase clinical trial in the drug development program. The results and the proposed pharmacometabolomic application framework in an early-phase clinical trial for the first analysis using metformin was recently published [51].

In the second report, the pharmacokinetics profiles for AP 1000 mg and AP 2000 mg will be presented. The results will include the dose-dependent effects of the dysregulated human metabolic pathways associated with the pharmacological effects. This report will suggest another application model for the pharmacokinetics and pharmacometabolomics study using multi-component herbal medicines in an early-phase clinical trial. Additional dose-dependent effects will be described in the report. Finally, the dysregulated human metabolic pathways associated with the diabetic effects will be compared for metformin and AP.

## 4. Discussion

This proof-of-concept study protocol aims to determine the pharmacokinetics and explore the metabolomics profiling of metformin and AP capsules for application in early-phase clinical trial. The protocol describes the conduct of clinical trials with comprehensive methods and Supplementary Documents that comply with the principle of Good Clinical Practice and relevant trial-related forms to record the clinical outcomes.

The pharmacokinetics and bioavailability study could determine the rate and extent of the drug being absorbed into the human blood circulation [27]. From the first metformin analysis dataset, the individualised peak plasma concentration obtained from the pharmacokinetics study will be used to explore the human metabolic pathways. This approach can identify the dysregulated human metabolic pathways associated with the pharmacological effect accurately based on the peak plasma concentration of the drug. Therefore, the combination of a pharmacokinetics and pharmacometabolomics study could complement the interpretation of the human metabolic pathways during peak plasma concentration.

In the second phase analyses, the two doses of AP capsules arms provide additional information about the pharmacokinetics profiles characteristic of the three biomarkers, andrographolide, neoandrographolide, and deoxyandrographolide. The pharmacometabolomic analysis for the two doses of AP capsules potential identify dose-dependent metabolic signatures with intense metabolic features at affected human metabolic pathways associated with the pharmacodynamic effects.

This study will employ a crossover design instead of the typical 6 + 2 dose escalation first-in-human study design to reduce the variability of the trial subjects in metabolomic study, shorten the trial duration, and maximise the resources to recruit different subjects. The study protocol is practical for institutional academic research compared to complex industry sponsor regulatory trials while complying with the Good Clinical Practice principle. This study potential provides a framework for the application of a pharmacokinetics and metabolomics approach in a phase one trial, which could reveal valuable drug intervention dysregulated human metabolic pathways or molecular drug effects through metabolomics analyses.

## 5. Conclusions

The proof-of-concept study protocol combines a pharmacokinetics and pharmacometabolomics study using metformin as the model drug, followed by AP in two doses in an early-phase clinical trial. The study protocol describes a crossover randomised controlled trial in healthy volunteers under the fasting condition with details of the trial procedures, data collection, data management, and statistical analysis. Two reports will be produced to describe the results of each analysis and propose an application model of the integration of pharmacokinetics and pharmacometabolomics in the drug development program. The incorporation of pharmacometabolomics in a pharmacokinetics study under a randomised controlled clinical trial will help to explore the metabolic pathways of drugs and herbal medicines in a drug development program.

## Figures and Tables

**Figure 1 jcm-11-03931-f001:**
[figure not shown]
Crossover, three—treatments, three—period clinical trial study design.

**Figure 2 jcm-11-03931-f002:**
[figure not shown]
The SPIRIT schedule of enrolment, assessment, and interventions.

**Figure 3 jcm-11-03931-f003:**
[figure not shown]
The diagram for dosing time, blood sampling, and urine sampling times in each period.

**Figure 4 jcm-11-03931-f004:**
[figure not shown]
The forms and templates of the data collection, management, and statistical analyses.

## Data Availability

Not applicable.
